## Discussion

The FIT-Stroke trial is a single-blinded multicentre trial in which 220 patients will be allocated to task-oriented CCT or usual face-to-face treatment at the nine participating rehabilitation centres, on the basis of a minimization procedure. The minimization procedure used for patient allocation has been recommended as a highly effective allocation method for randomized controlled trials[27].

The main characteristics of the task-oriented CCT programme are the progressive intensity and task specificity of the workstations used. The eight different functional workstations used in the trial have been found to be meaningful and relevant to patients' needs, goal-oriented, challenging, and feasible (i.e., not to easy and not to difficult). As such, the programme builds heavily on the existing evidence that intensity of practice[12,57] as well as task specificity[13,57] are the main drivers of gait improvement. After reviewing 14 trials, French and colleagues[13] showed that repetitive task-oriented training resulted in modest improvement in lower limb function. Although the authors claimed that the repetitive lower limb training was sufficient to influence daily living functions, no evidence was found that the effects of repetitive training were sustained once training had ended. In order to fill this gap in existing evidence, the FIT-Stroke trial will have a follow-up of three months to investigate the possible wash-out effects of the task-oriented CCT programme.

Recently, Wevers and colleagues showed significant effects in favour of task-oriented CCT for walking distance, gait speed and a timed up-and-go test in their systematic review of randomized controlled trials including 307 participants[19]. The intensity of task-oriented CCT ranged from 4 weeks (3 times a week for 60 minutes)[24] to 19 weeks (3 times a week for 60 minutes)[58]. Therefore, we assume that in the present study, a training schedule of 24 sessions each lasting 90 minutes within 12 weeks will be sufficient to achieve functional gains in gait and gait-related activities. Unfortunately, most studies included in the above meta-analysis were small and statistically underpowered, ranging from 12[24] to 91[59] participants, which suggests that larger trials are warranted. Only one study[60] included in the meta-analysis investigated the effects of task-oriented CCT within the first 6 months post stroke. Interestingly, this study found a larger effect size than those that investigated effects in chronic stroke. However, none of the included studies compared the cost-effectiveness of task-oriented CCT with that of usual care, which is particularly important in view of the burden of health care costs for stroke and attempts to save costs in stroke management. This aim is in line with the views of the American Hearth Association (AHA), which recently recommended that fundraisers and researchers should conduct cost-effectiveness studies in the growing and ageing stroke population[8]. By including 220 patients within the first months after their stroke and focusing on cost-effectiveness as well as health-related quality of life, we hope to fill the existing gaps in stroke rehabilitation research.

Finally, we will give special attention to the generalizability of the effects of this physical intervention to psycho-social outcomes, like fatigue, anxiety and depressive symptoms. Including a large population will enable us to conduct sub-analyses on smaller groups for these less frequent outcomes. The larger population will also enable us to record the effects on other less frequent outcomes like recurrent stroke, and co-morbidities like cardiac problems. Ongoing participation in physical activity may also reduce the prevalence of vascular risk factors and so reduce the risk of coronary heart diseases and recurrent strokes[10,11]. For example, a meta-analysis[61] has demonstrated that increased physical activity improves cardiac performance and exercise capacity in patients with heart failure.

In conclusion, task-orientated CCT holds great potential for the rehabilitation of people after stroke, allowing the training schedule to be customized to the individual status of each participant. We hypothesize that task-oriented CCT will be equally effective in improving gait and gait-related activities in stroke as face-to-face therapy alone, or even more so. The FIT- Stroke trial will give us a unique opportunity to study the effects of task-oriented circuit class training in a large and carefully designed trial. The first results of the study are expected in August 2011.

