### Procedure

Patients will be stratified by rehabilitation centre and subsequently randomized to task-oriented CCT or to individual face-to-face physiotherapy, using an 'online' minimization procedure[27]. The intervention period will be 12 weeks and measurements will be taken at baseline, 6, 12, 18 and 24 weeks. All outcomes measured at baseline, 12 and 24 weeks will be assessed in face-to-face meetings by an independent researcher, blinded for treatment allocation, whereas at 6 and 18 weeks, a restricted set from the test battery will be assessed by semi-structured telephone interviews (Figure 1).

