### Intervention group

Patients assigned to the intervention group (two participants or more) will receive a 90-minute structured progressive task-oriented CCT programme twice a week over a twelve-week period (24 sessions). The programme includes 4 stages: (1) warming up (5 minutes), (2) circuit class training (60 minutes), (3) evaluation and a short break (10 minutes) and (4) group game (15 minutes). The training programme includes 8 different workstations, intended to improve meaningful tasks related to walking competency, such as balance control, stair walking, turning, transfers and speed walking. The eight workstations incorporated in the circuit are: (1) standing and reaching; (2) stair walking including transfer; (3) walking and picking up various objects from the ground; (4) kicking a ball; (5) stepping up and down; (6) walking course with obstacles; (7) transfers (lying to standing and sitting); and (8) speed walking. Graded progression will be achieved by (1) increasing the difficulty of the task; (2) adding weights; or (3) increasing the number of repetitions. No special (fitness) equipment is needed to perform the tasks. Each workstation will be done for 3 minutes, followed by 3 minutes of rest and 1 minute to change to the next workstation. The participants will complete the exercises in pairs, where one does the exercise while the 'partner' has a rest period and helps the other by keeping track of the number of repetitions and stimulates him/her to perform at their best. Time will be kept by the supervisors. The precise composition of the treatment package for each patient, in terms of appropriate selection of type of workstation, number of repetitions and intensity, will be determined at baseline, based on patients' profiles in terms of muscle strength, physical fitness and mobility status. All patients will keep an activity log in which they record the number of repetitions at each workstation during the sessions, which they will then use as feedback in the next session. The one-hour session of workstation training will be followed by a 15-minute group game, in which the whole group performs a game to improve walking competency. Games will vary across the sessions. Options include a game in which walking tasks are combined with a cognitive task, or a game consisting of fast walking and changing directions. Ball games can of course be used as well, as long as they serve to train walking performance. Incidents that occur during the training sessions (e.g. falls) will be reported by the supervisors to the independent investigator and registered in a falls diary. Patients who are allocated to the intervention group will receive no other physiotherapeutic treatment for the lower extremities.

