
### Control group

Patients who are allocated to the control group will receive regular care and will therefore be referred to the usual outpatient face-to-face treatment given by physiotherapists at the rehabilitation centres. Treatment designed to improve standing balance control, physical condition and gait performance will be provided. No additional restrictions will be imposed with respect to content, time or duration of the therapy.

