### Compliance

In order to conduct this trial uniformly in nine different rehabilitation centres, all supervisors have to be trained in a one-day course before the FIT-Stroke trial starts. In the past year, about 60 physiotherapist and sports therapists have been trained. Each therapist has been informed about: (1) the criteria for recruitment of candidates discharged from the inpatient rehabilitation centre; (2) the aims, design and measurement instruments of the FIT-stroke trial, (3) how to fill in the patients' training diaries, (4) the focus and content of the task-oriented CCT programme and (5) how to stimulate the participants to maintain an active lifestyle after the task-oriented CCT sessions end. After practical training about applying and adapting the eight workstations and how to intensify the workload progressively, all trained supervisors were able to conduct the intervention in a standardized manner. Subsequently, all other physiotherapists, sports therapists and physicians who will be involved in the treatment of the included stroke patients were informed about the content of the intervention by means of presentations in each rehabilitation centre. In order to prevent contamination, therapists were instructed not to change the treatment procedures of the usual face-to-face physiotherapy during the trial. Finally, all managers of rehabilitation centres were asked not to change treatment policies during the FIT-Stroke trial. In the coming years, retraining activities will be organized and an independent investigator ([name]) will monitor on a regular basis whether the content of the task-oriented CCT and the usual physiotherapy are being implemented as intended in the nine rehabilitation centres.

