#### Diaries

Finally, each patient will be asked to keep a cost diary, which will be used to assess medical consumption in both arms of the study. Patients will be asked to record their medical consumption (for example visits to a general practitioner, hospital visits, medication intake) each week. In addition, they will be asked to record their level of activities during the day (activity log) as well as special events (e.g. falls). This dairy will be kept daily for 12 weeks. After 12 weeks, the patients will be asked to continue recording weekly until 24 weeks after inclusion.

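### The protocol does not say when control physiotherapy ends, so the 24-week between-arm difference does not by itself measure wash-out or persistence of CCT

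*Protocol article*

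**What the plan says.** The Discussion cites a review of repetitive task training in which "no evidence was found that the effects of repetitive training were sustained once training had ended". To fill that gap, it continues, "the FIT-Stroke trial will have a follow-up of three months to investigate the possible wash-out effects of the task-oriented CCT programme".

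The treatment rules for the two arms are set out elsewhere:

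- **Procedure:** "The intervention period will be 12 weeks and measurements will be taken at baseline, 6, 12, 18 and 24 weeks". This follows directly on the description of randomisation to both arms.
- **Intervention group:** CCT is given twice weekly for 12 weeks, 24 sessions in all. In addition, "Patients who are allocated to the intervention group will receive no other physiotherapeutic treatment for the lower extremities". No time limit is attached to that bar.
- **Control group:** patients are referred to usual outpatient physiotherapy. "No additional restrictions will be imposed with respect to content, time or duration of the therapy".
- **Data analysis:** a random coefficients model on the repeated measurements evaluates the difference between the arms.
- **Diaries:** medical consumption and activity are recorded in both arms. "After 12 weeks, the patients will be asked to continue recording weekly until 24 weeks after inclusion".

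**The concern.** Wash-out is a question about what happens to an effect after training stops. A between-arm difference answers it only if therapy after that point is absent, or alike, in both arms. Here training has a stated end in one arm only. A control patient may, on the wording, still be in physiotherapy at week 24. A CCT patient has finished the programme and may or may not be allowed other lower-limb physiotherapy by then.

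A smaller difference at week 24 than at week 12 would then have two explanations: CCT gains faded, or controls went on gaining. A stable difference is ambiguous too, since losses in the CCT arm could be matched by losses in controls whose therapy had stopped. What is at stake is the sentence the trial report may write about durability, not the test of the primary outcome.

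**Working it through.** **1. Stated end of treatment, side by side**

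| | CCT arm | Control arm |
|---|---|---|
| Allocated therapy ends | After 24 sessions, week 12 (Intervention group) | No end stated (Control group), unless the 12 weeks under Procedure apply here too |
| Other lower-limb physiotherapy, weeks 13–24 | Barred, or bar lifted at week 12: not stated | Not restricted |

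Procedure and Control group can be read together in two ways. Either the 12 weeks cover both arms, and the open duration means only session length or intensity within them; or the 12 weeks describe CCT, and usual care runs as long as the centre decides. The text does not settle which.

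**2. What the week-24 difference contains**

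Let R be the part of a week-12 CCT advantage still present at week 24, and G the extra control gain from therapy continued after week 12. Recovery common to both arms cancels. Then

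D24 = R − G.

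Take the 5-point SIS mobility difference from Power analysis as the week-12 advantage, purely as a scale. R and G are assumed values; the protocol gives neither.

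| | G = 0 | G = 2.5 | G = 5 |
|---|---|---|---|
| R = 5 (all kept) | 5 | 2.5 | 0 |
| R = 2.5 (half kept) | 2.5 | 0 | −2.5 |
| R = 0 (none kept) | 0 | −2.5 | −5 |

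A difference of 0 at week 24 fits full retention, half retention or complete loss. One number cannot identify two unknowns.

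For smaller assumed gains with full retention (R = 5):

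- G = 1: 5 − 1 = 4, an apparent loss of 1/5 = 20%
- G = 2: 5 − 2 = 3, an apparent loss of 2/5 = 40%
- G = 3: 5 − 3 = 2, an apparent loss of 3/5 = 60%

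These percentages are the assumption divided by 5. They show how the misreading works and are not estimates.

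**3. Precision**

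The planned size is consistent on dropout: 2 × 99 = 198, and 198/0.90 = 220. With 99 per arm and the planning SD of 14, the 95% half-width of an unadjusted single-visit difference is 1.96 × 14 × √(2/99) = 3.9 points. That exceeds each of the 1- to 3-point shifts above, so shifts of that size would be hard to see in one visit's contrast. A larger sample would narrow the interval but would not separate R from G.

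**The case against.** Four arguments on the other side deserve weight.

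- **The 12-week intervention period may cover controls.** It may, and then much of the problem disappears. But the Control group section leaves duration open, so the two statements need reconciling. The text permits control therapy after week 12; it does not say that it occurs.
- **No rule says that wash-out will be judged from the 24-week difference.** Correct. The Discussion says only that wash-out will be investigated, and the visits at 12, 18 and 24 weeks also show the course within the CCT arm. It would be an inference to say that the plan commits to the faulty reading. The described model, however, targets differences between arms, and nothing warns against that reading.
- **Wash-out is a secondary purpose, and unrestricted usual care is a legitimate pragmatic comparator.** Both are true. This limits the weight of the point.
- **A full protocol or analysis plan may tabulate therapy received.** It may, and the absence of such a table here is not the complaint. The complaint is that a purpose stated in the article is not delivered by the treatment rules stated in the same article.

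A reader might go further and infer that neither arm is off treatment after week 12, because supervisors are taught "how to stimulate the participants to maintain an active lifestyle after the task-oriented CCT sessions end". The protocol does not support this. Supervised CCT stops. The phrase describes the content of a one-day staff course, no contact after week 12 is mentioned, and the encouragement could be given during the sessions. If patients stay active because of the programme, that is arguably part of its lasting effect and not a bias in measuring it.

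**Conclusion.** The point holds in a limited form. As written, the treatment rules fix an end for CCT and none clearly for control physiotherapy, so the week-24 between-arm difference cannot by itself be read as persistence or wash-out of CCT. It should not be inferred that the week-24 comparison is invalid: it remains a randomised comparison of two care policies.

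The size of any distortion is unknown. It depends on how many controls continue therapy after week 12 and what they gain from it, and the protocol gives neither. If control therapy in practice stops at about week 12, or if CCT patients then receive similar care, the ambiguity is small. The issue is minor, but it changes what may be concluded about durability.

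**What to change.** 1. Reconcile Procedure, Intervention group, Control group and Discussion, so that the text states whether the 12-week period applies to controls and whether the bar on other lower-limb physiotherapy in the CCT arm continues after week 12. Which rule applies is for the investigators; the need is that the passages agree.
2. Describe the week-24 contrast as the difference between the two care policies 12 weeks after CCT ends.
3. Beside the 24-week result, report physiotherapy received and activity by arm for weeks 1–12 and 13–24, from the diaries already kept. Two cautions apply. Recording changes from daily to weekly at week 12, so comparisons between arms within a period are safer than comparisons between periods. It should also be confirmed that the diary's paramedic item identifies physiotherapy.
4. Present the week 12 to 24 course within the CCT arm as descriptive and non-randomised.
5. Claim that effects persisted or faded after training only if the diaries show that therapy after week 12 was little and similar in both arms.

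The cost is a change of wording and one descriptive table, with no new data collection and no change to treatment. The downside is a more modest claim about durability.
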